#### Examining changes in myelinisation distributions in frontal-striatal regions from the Structure Learning training

Parameter maps will be generated based on Weiskopf et al [48]. After normalisation and smoothing, we will extract mean MPM measures from masks of ICA components derived from the rs-fMRI GICA analysis. Difference scores from MPM parameter maps will be correlated with behavioural indexes computed from Structure Learning training to investigate the relationship between myelinisation distributions with how one performed during the Structure Learning training. We are expecting significant correlations to manifest in cortical regions. 

### Methods for additional analyses (e.g. subgroup analyses) {20b}

#### Examining strategy-associated changes during Structure Learning training in cognitive flexibility and functional connectivity

In addition to the planned analyses mentioned previously, we will also explore data-driven approaches with rs-fMRI data. These exploratory analyses (connectome-based predictive modelling) can complement results from the planned analyses and ascertain whether findings from both approaches corroborate. The Structure Learning training protocol that we are implementing is a novel cognitive training approach. Thus, our hypotheses are formulated based on limited past studies and it is hard for us to make predictions on the type of decision strategies that participants will engage in and how this will affect our behavioural and neuroimaging outcomes. Published studies on Structure Learning generally suggest the usage of two main strategies as an individual goes through Structure Learning training. Hence, we will also conduct subgroup analyses to examine the impact of different decision strategies on cognitive flexibility primary outcomes and functional connectivity patterns derived from rs-fMRI.

#### Subgroup categorisation of decision strategies

We will categorise participants of the Training group into three groups, i.e. maximising, matching, random based on their mean strategy ICD across the training sessions which indicates the strategy that they primarily engaged in. Criterion for the strategy group categorisation will be based on similar past studies [33, 34, 43, 69]. However, due to sample size constraints, minor modifications may be made to ensure that each strategy group has adequate participants to perform group comparisons. We will then examine how these different strategy groups can affect functional connectivity pattern changes and cognitive flexibility outcomes.

### Methods in analysis to handle protocol non-adherence and any statistical methods to handle missing data {20c}

Any deviations from the protocol due to human or technical errors are noted down in an Excel sheet and corrected whenever possible. Missing data in behavioural outcomes are accommodated with the use of mixed effects models. Data imputation will be performed only if we have more than 20% of data missing for any one of the behavioural measures. We will not perform any data imputation for neuroimaging data. Instead, any unusable data in a particular MRI modality will be discarded and neuroimaging data from other intact MRI modalities kept for analyses. Hence, the eventual number of participants used for analyses in the different neuroimaging modalities may differ. Finally, all data from any participants who have withdrawn from the study will be excluded from the data analyses.

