### Criteria for discontinuing or modifying allocated interventions {11b}

The current study recruits only healthy participants. Therefore, the intervention will only be discontinued if the participant chooses to withdraw from the study or if there is an unexpected scheduling conflict that prevents them from committing to the remaining experiment sessions.

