### Strategies to improve adherence to interventions {11c}

The Structure Learning training programme is rigorous as it involves 1-h daily training for at least 13 consecutive days and can impact participants’ adherence to it. The study team has implemented the following steps to improve adherence and minimise participant’s withdrawal from the study. Firstly, the training is guided remotely, and participants do not need to attend training sessions physically. This enables greater flexibility in the scheduling of training sessions and ensures that training occurs in a comfortable and familiar setting for the participants. The remote-guided protocol used for the Structure Learning training programme is based on Leong et al. [44] who demonstrated comparable data quality between laboratory-based and remote-guided studies. Secondly, we also provided a comprehensive study timeline to participants at the first point of contact during the informed consent session to ensure participant’s availability for all sessions. Advance scheduling is done for all sessions to ensure that participants can plan their schedule accordingly in consideration of the sessions. Thirdly, we also ease the scheduling of sessions by assigning the same experimenter to each participant throughout the training phase. Lastly, continuous monitoring of participants’ attendance and training progress via a master schedule documenting all sessions and the experimenters-in-charge also enable prompt identification of any non-adherence and facilitate timely communication and support between experimenters. Besides appropriate arrangements to ease scheduling, we also monitor participant’s arousal, valence, and sense of control via the Self-Assessment Manikin [45] at the start of each training session. We can then quantify possible psychological effects from the training sessions and rectify any potential issues.

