### Relevant concomitant care permitted or prohibited during the trial {11d}

The current study targets healthy adults unlike clinical trials that involve clinical populations. Hence, there are no alternative interventions for participants. Nonetheless, to ensure that any observed effects can be unequivocally attributed to the Structure Learning training programme, participants are asked to avoid engaging in any other intervention studies or brain stimulation research during their study involvement. We will proceed to withdraw a participant once we know that they are concurrently involved in other intervention studies or brain stimulation research to maintain the integrity of the data.

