
### Participant timeline {13}

Participants are recruited from various social media platforms. In addition, we also contacted higher education institutes such as polytechnics and universities in Singapore to send out email recruitment advertisements. Individuals who express interest in participating will be asked to complete an Eligibility Screening Questionnaire. Eligible participants who meet the predefined inclusion and exclusion criteria are contacted through email and invited to take part in the study. Participants follow the same schedule shown in Table 3, with slight differences depending on their group assignment. The study commences with the baseline assessments, comprising Baseline Cognitive Session 1 and Pre-test Social Questionnaires. Once the baseline cognitive measures have been administered, participants are pseudo-randomised into either the Training or Control groups. Participants then proceed to complete the remaining sessions outlined in Fig. 3. During the cognitive sessions, participants complete a comprehensive battery of cognitive tasks and questionnaires. In the pre-test, we focus on measuring various traits such as language skills, numeracy skills, and non-verbal intelligence. In the post-test, we administer critical outcome measures such as cognitive flexibility, working memory, inhibition, and other secondary behavioural measures. MRI sessions during both pre-test and post-test employ the same MRI scan protocol. During the 2-week interval between pre- and post-intervention phases, participants in the Training group additionally undergo a minimum of 13 Structure Learning training sessions. A detailed list of tasks that each participant will undergo at each session of the study can be found in appendix B from the supplementary information. The study is projected to span a total of 10 weeks. A time commitment of 12 and 32 h is needed for participants in the Control and Training groups respectively.

**Table 3 Tab3:** Participant schedule

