### Sample size {14}

The present study is designed as a scoping study to provide a good estimate of the sample size needed to detect the actual training effect in subsequent studies. Hence, sample size estimation may not be that accurate since the training programme implemented in the current study is novel and effect sizes can be hard to estimate.

Behaviourally, the sample size estimation is based on a statistical power of 0.8 with type I error rate held at an alpha level of 0.05. The estimates of statistical power are all made based on a balanced sample (equal sample size for all conditions) with a 2 × 2 mixed design with one between-subject factors (Group: Control and Training) and one within-subject factor (Time: Pre-test and Post-test). The detection of a Group × Time interaction with a small effect size of *d* = 0.25 and an assumed low population correlation of 0.3 between levels of the within-factor, Time, would need 46 participants for each level in the between-factor, Group.

Sample size estimation is done separately for the different neural measures. In healthy adults, GABA spectral peak height relative to that of water in the PFC generally showed a standard deviation of 0.24. Based on past MRS studies that measure GABA in DLPFC, the detection of a small effect size in GABA spectral peak height relative to water would need 50 participants for each group. In rs-fMRI, based on a reported correlation of *r*= 0.46 between the functional connectivity of corticostriatal networks and performance measures for Structure Learning [33], we derived a sample size of 35 participants per group to detect significant correlations. Finally, as MPM is still a relatively novel scan sequence used to quantify microstructures within the brain, prior data is hence unavailable for us to perform any power computation and sample size estimation. Instead, we sampled published MPM studies that employed similar methodological analyses [52, 53] and opted for an average sample size of 34 participants per group.

Based on sample size computation of the various measures, we opted for the highest sample size of 50 participants per group to ensure sufficient statistical power to detect significant effects in all measures. With a data attrition rate of 20%, the required sample size is set at 60 participants per group.

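### Excluding every value from anyone who withdraws departs from analysis as allocated, discards usable data and leaves the group comparison open to bias of unknown size and direction

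*Protocol article*

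**What the plan says.** The rule is in Protocol article, section {20c}: "all data from any participants who have withdrawn from the study will be excluded from the data analyses". Nothing there or elsewhere restricts it to withdrawals before allocation, to withdrawn consent for data use, or to values not yet collected. No analysis of all participants as allocated is described.

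The same section says "Missing data in behavioural outcomes are accommodated with the use of mixed effects models", and it allows imputation only when more than 20% of a behavioural measure is missing.

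Withdrawal after allocation can arise in several ways:
- Section {11b}: the participant chooses to leave, or the intervention stops "if there is an unexpected scheduling conflict that prevents them from committing to the remaining experiment sessions".
- Section {11d}: the investigators act. "We will proceed to withdraw a participant once we know that they are concurrently involved in other intervention studies" (or in brain stimulation research).

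On burden, section {13} states: "A time commitment of 12 and 32 h is needed for participants in the Control and Training groups respectively". Section {11c} describes the programme as "1-h daily training for at least 13 consecutive days" and accepts that this can affect adherence.

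Trial design {8} describes a superiority trial. Most outcomes are taken only at post-test, and that section justifies the post-test comparison by the matching of the groups on age, sex, intelligence and baseline cognitive flexibility.

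**The concern.** Matching at allocation protects the comparison only if the groups analysed are the groups allocated. Removing people because of something that happens afterwards replaces them with groups selected by staying in. Most outcomes have no baseline value of their own, so any resulting imbalance on them cannot be seen or adjusted for directly.

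Only the Training arm has daily sessions to sustain or to clash with other commitments. It is therefore plausible that withdrawal differs by arm. It is also plausible that people who cannot keep up two weeks of daily training differ in the abilities being measured. If both hold, a difference between the remaining participants is partly a selection effect.

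The rule also weakens the plan's own missing-data methods. Withdrawers cannot contribute to the mixed models. On a plain reading they also leave the count of missing values, so the 20% trigger for imputation might not be reached even with heavy dropout.

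Sample size {14} says that the study is meant to supply an effect estimate for sizing later studies, so a distorted estimate would carry forward.

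**Working it through.** **1. Burden by arm (section {13}).** 32 / 12 = 2.67, a difference of 20 h. The 32 h does not rebuild from the sessions: 12 h plus 13 to 14 one-hour sessions is 25 to 26 h, a ratio of 25/12 = 2.1 to 26/12 = 2.2. On either count, Training asks for more than twice the time.

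**2. The plan's own allowance (section {14}).** The plan says "we opted for the highest sample size of 50 participants per group", and then "With a data attrition rate of 20%, the required sample size is set at 60 participants per group". The 60 reproduces as 50 × 1.20. A 20% loss is 0.20 × 60 = 12 per group, or 24 of 120. This is data attrition. Interim analyses {21b} shows that unusable scans also reduce the sample, so the 20% is not a withdrawal rate.

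**3. What the rule removes, by time of leaving (section {12} and Table 3).** Training runs in weeks 6 and 7, the post-test scan and social questionnaires in weeks 8 and 9, and post-test cognitive sessions 3 and 4 in weeks 9 and 10.

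| When the participant leaves | What the exclusion removes |
|---|---|
| Before allocation | Nothing that matters to the group comparison |
| During training, does not return | No post-test outcome exists; pre-test values on measures taken twice (Colour Shape Task (CST), Raven's matrices (RAPM), social and decision measures, MRI) and the baseline predictors age, sex, CST and RAPM are lost |
| Stops training but could attend post-test | All of the above, plus every post-test outcome, if classed as withdrawn |
| After the post-test scan or session 3, before session 4 | Post-test outcomes already collected |
| Withdrawn by the investigators after allocation | Whatever had been collected by then |

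**4. Illustration of completers-only bias.** The documents give neither withdrawal by arm nor withdrawers' scores, so every rate and gap below is an assumption. Let a proportion p of an arm withdraw, with a mean g SD below that arm's overall mean. Completers then lie g × p/(1 − p) above it. With no training effect,

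bias = g × [pT/(1 − pT) − pC/(1 − pC)].

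| pT | pC | Bracket | g = 0.3 | g = 0.5 |
|---|---|---|---|---|
| 25% | 10% | 0.333 − 0.111 = 0.222 | 0.067 | 0.111 |
| 30% | 5% | 0.429 − 0.053 = 0.376 | 0.113 | 0.188 |
| equal | equal | 0 | 0 | 0 |

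A second form takes g as the gap between withdrawers and completers, so that bias = (pT − pC) × g. Let 24 of 120 withdraw, and let g run from 0.25 to 1.0 SD:
- Equal by arm: 0.
- 2:1 (26.7% against 13.3%): 0.03 to 0.13 SD.
- In proportion to stated hours, 2.67:1 (29.1% against 10.9%): 0.05 to 0.18 SD.

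Positive values favour Training. If withdrawers score above those who stay, the sign reverses.

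**The case against.** Several points on the other side are sound.

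- **Outcomes that were never collected.** A reader might infer that the 0.07 to 0.19 SD is the effect of this one sentence. It is not. It is the bias of any completers-only comparison under the assumed rates. Someone who leaves in weeks 6 or 7 has no session 3 or 4 outcome to exclude, and removing the sentence alone would not supply one. The part due to the rule itself cannot be quantified from the documents.
- **Direction.** A reader might infer a built-in advantage for Training. The documents support a risk only. Section {18b} says that the maximum commitment is disclosed at consent in order to reduce withdrawal after assignment, and section {11c} adds remote sessions and advance scheduling. These may narrow the difference in withdrawal, although they are not an analysis remedy.
- **Contradiction.** The mixed-model sentence might seem to contradict the exclusion. It can be read consistently as covering gaps in participants who stay. The multivariate mixed model on combined executive-function measures could also borrow across tasks, but not for people already removed.
- **Benchmark.** It is tempting to divide the bias by the planned d = 0.25. That figure is a Group × Time interaction effect and the bias is a post-test difference, so the ratio has no clear meaning.
- **Wording.** The text excludes data from analysis. It does not say that records are deleted.
- **Purpose and timing.** The study calls itself a scoping study. The protocol version is dated 11 May 2023 and collection was projected to end in June 2023, so there was little room to bring back earlier non-completers.

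What remains is an unqualified rule, stated in the text rather than left to another document, with no as-allocated analysis beside it.

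**Conclusion.** The concern holds as a departure from analysis as allocated and an avoidable loss of collected data, with possible bias whose size and direction the documents do not allow anyone to determine. Bias requires withdrawal that relates to outcome and differs between arms in rate or in kind. The stated burden of 32 h against 12 h and the acknowledged adherence risk make this plausible, but no withdrawal figures are given.

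Under the assumed differential withdrawal, the illustrative bias of a completers-only comparison is about 0.07 to 0.19 SD; with equal withdrawal of similar participants it is zero. The rule's own contribution falls on partial post-test data, twice-measured outcomes, people who stop training but could still be assessed, and the baseline information needed for imputation. Keeping those data removes the exclusion by rule. Outcomes that were never collected will still need an explicit missing-data assumption.

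**What to change.** Replace the exclusion sentence in section {20c}, and any matching text in the SAP, with: *All allocated participants are analysed in the group allocated, using every value collected before withdrawal; data are removed only where the participant withdraws consent to their use.*

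Then add:
- For missing post-test outcomes, multiple imputation from group, age, sex, baseline CST and RAPM, or retention of withdrawers in the planned multivariate mixed model.
- A delta-adjusted sensitivity analysis, with the shift allowed to differ by arm, since withdrawal may depend on unseen outcomes.
- A count of missing values that includes withdrawers among all allocated participants.
- Training completers as a secondary set, labelled as such.
- Withdrawals reported by arm, timing and reason.
- For anyone still in follow-up who stops training, an offer of the post-test sessions already scheduled.

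The cost is a wording change and a little more analysis work. Any extra visits would be few, because collection was close to its projected end. The estimated effect may be slightly smaller.

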### Plans to give access to the full protocol, participant-level data, and statistical code {31c}

The full protocol including MRI processing pipelines and statistical code will be shared on open science platform (https://osf.io/) and/or GitHub. Pre-prints of findings will first be uploaded to preprint servers, such as bioRxiv (https://www.biorxiv.org/) and then published to peer-review journals. All data (both behavioural and neuoimaging data) generated from this research are subjected to restrictions by the National Research Foundation (NRF), Singapore and Nanyang Technological University (NTU), Singapore, and hence not publicly available. Any data required to support the protocol, are, however, available from the authors upon reasonable request and with the permission of both NRF and NTU.

## Oversight and monitoring

### Composition of the coordinating centre and trial steering committee {5d}

The researchers from the NTU-CLIC are responsible for the study’s day-to-day data collection, data analysis, and organisational supports to ensure the smooth running of the study. The principal investigators have a monthly meeting with the researchers, during which they are updated on the study’s progress and to discuss data analysis plans.

### Composition of the data monitoring committee, its role and reporting structure {21a}

N/a. Since the current study implements cognitive training, there is no risk of causing clinical disturbance; hence, we decided to not have a data monitoring committee.

### Adverse event reporting and harms {22}

Adverse events are collected and assessed on its severity by the principal investigator and researchers of this study. Should there be an incident of a serious adverse events or an unanticipated problem during the data collection process, the principal investigator of the study will report it to the NTU-IRB by submitting the details of the event in an Incident Report Form. An unanticipated problem will also be submitted to the IRB if there is any unforeseen harm that may or may not occur that is inconsistent with the risk levels previously approved for the study. This includes issues of confidentiality and complications in using the study’s materials and devices.

### Frequency and plans for auditing trial conduct {23}

There was an IRB compliance auditing check requested by NTU-IRB on 22 July 2022. All research team members were required to attend and display all consent forms, every member’s research training certificates, and data management method for a check. Access to data and personal information was also checked to ensure the adherence of NTU-IRB policy.

### Plans for communicating important protocol amendments to relevant parties (e.g. trial participants, ethical committees) {25}

Protocol amendments to the study are only submitted to the NTU-IRB via the university’s ethical review management portal. The ethics committee from the university’s research integrity and ethics office review approve or request for additional changes to the submission via this portal as well. Once submitted, all investigators and key personnel of the study have been informed of this submission via email. After approval, the investigators and key personnel are notified via email and the study protocol on the university’s ethical review management portal is updated to include the amendment changes as an updated version. This study protocol as well as the email approval letter have been downloaded and stored in a cloud-based storage service for record keeping purposes.

